### Objectives

2.2

The aim of this study is to assess whether increasing the time interval between rESWT sessions extends the therapeutic benefits on spasticity to be prolonged in patients with CP. The specific objectives are: (a) to evaluate whether the effects of the time factor imply an improvement in spasticity assessed with the Modified Tardieu Scale, (b) to evaluate whether the effects of the time factor imply an improvement in the clinical and functioning aspects of the person, assessed with the Goal Attainment Scaling, (c) to evaluate whether the effects of the time factor imply an improvement in the functional response of improving the gait and the overall patient mobility, (d) to evaluate whether the effects of the time factor imply a decrease in muscle contracture produced by spasticity and assessed with point shear wave elastography using musculoskeletal ultrasound, (e) analyze whether the patient’s age influences the treatment results, (f) analyze whether the level of gross motor function classification influences treatment results, (g) know the patient’s satisfaction regarding the different interventions with shock waves, (h) record possible adverse effects of interventions.

### Setting study

2.3

The study will be conducted at Fundació Aspace Catalunya, a non-profit organization founded in 1961. The objectives of this entity have always been to promote services for the research, diagnosis, rehabilitation, and education of people with CP or other developmental disabilities, as well as their families. It was a pioneer in Spain in the treatment of patients with brain damage, mainly congenital, and especially in CP.

### Participants

2.4

The patients eligible to participate in the study will be, in all cases, from the foundation and will be selected by the medical rehabilitators of the organization. Once it is confirmed that participants meet the selection criteria (Table 2), they will be provided with a letter that informs them about the purpose, objectives, necessity of the study, its duration, procedures, and potential benefits and risks. Those patients who express their willingness to participate will be given the informed consent form to accept the study conditions. In the case of minor patients, even if the informed consent is signed by their legal representatives, it must be signed in their presence and with their consent. Patients and/or legal representatives will also be informed of their rights and the option to withdraw from the study at any time without providing reasons. A withdrawal/abandonment form will be provided to them.

**Table 2 tab2:** In-and exclusion criteria.

Inclusion criteria	Exclusion criteria
Patients with a CP classified as spastic	Having received shockwave therapy treatment in the Triceps Sural or any other muscle of the lower extremity within the 6 months prior to the study
Patients of both sexes	
Age between 4 and 45 years	Having received botulinum toxin treatment and/or focal intramuscular treatment with phenol or alcohol in the Triceps Sural or any other muscle of the lower extremity within the 6 months prior to the study
Spasticity in the Triceps Surae muscle	
Who present a Gross Motor Classification (GMFCS) level l and ll	Any contra-indication for the specific treatment (e.g., coagulopathies, malignancies in treated area)
With unilateral or bilateral involvement	Patients who have undergone surgical intervention for orthopaedic foot deformities in the past year
Having obtained the informed consent signed by the participant or their legal guardian	Fixed deformities in the ankle joint
	Clinical signs of myopathy and neuropathy

### Randomization, blinding and treatment allocation

2.5

Once the participants and/or their legal representatives have signed the informed consent, they will be randomized through an equally probable algorithm using the statistical program R software to determine which of the 3 interventions they will be assigned to. Because the age range for the inclusion of participants is wide, it will be minimized with a stratification of the sample into three age ranges. From 4 to 15 years, from 16 to 30 years and over 30 years. In this study, the evaluating physiotherapist and their assistant will be blinded throughout the entire intervention. The data analyst will also be blinded. Due to the nature of the technique employed in the study, neither the patient nor the professional administering the rESWT sessions can be blinded. The concealment of the assignment will be centralized through one of the researchers, who will be responsible for communicating the assigned intervention to the participants and/or their families via a telephone call. The assignment outcome will be recorded in the corresponding section of the data collection notebook, which will not be accessible to the evaluating physiotherapist. This section of the data collection notebook will be integrated into the complete patient dossier once the follow-up for the last patient is completed, ensuring that the evaluator does not have access to this information during the course of the study. The evaluating physiotherapist will always be the same and will be unaware of the origin of the intervention group to which the patient belongs. Neither the evaluating physiotherapist nor their assistant will inquire about the treatment received, nor will they ask any questions to the doctors, physiotherapists in the center, or patients regarding the intervention groups. Instructions will also be given to the patient and their family not to discuss the received treatment during assessments. Interventions and evaluations will take place in different locations within the center.

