### Outcome measures

2.7

Primary outcome measures: Spasticity of the treated muscles assessed with the Modified Tardieu Scale (MTS). Secondary outcome measures: Goal Attainment Scale (GAS), Timed Up and Go Test (TUG), 10 Meter Walk Test (10-MWT), Point shear wave elastography (pSWE), satisfaction with the therapy, and adverse effects. Prior to the first rESWT session, the blinded evaluating physiotherapist and his assistant will conduct a baseline assessment (t0) of all outcome variables and other aspects deemed appropriate as reference for assessing goal achievement. These assessments will be repeated across all intervention groups at 3 weeks from the start of treatment (t1), 5 weeks from the start of treatment (t2), 9 weeks from the start of treatment (t3), 12 weeks from the start of treatment (t4), and 24 weeks from the start of treatment (t5).

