#### Goal attainment scaling

2.8.2

The Goal Attainment Scaling (GAS) is an individualized and patient-centered scale in which specific goals (one main and one secondary in our case) are proposed with concrete expectations for each patient. It provides two types of information: quantitative (assessment of success) and qualitative (what the patient aims to achieve). Once the objectives of shock wave application are agreed upon with the patient and/or family, such as improving function, gait, pain, perceived spasticity sensation, or enhancing orthosis tolerance, improvement expectations will be determined for each objective. It will be assessed whether these expectations have been met (0), are better (+1), much better (+2), worse (−1), or much worse (−2) than expected. It is a highly dynamic scale that allows quantifying any set objective. It is possibly the scale that best aligns clinical practice with patient expectations (26).

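### Allocation is scheduled before baseline, and nothing withholds its disclosure until the GAS goals and walking-test baselines are fixed

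*Protocol article*

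**What the plan says.** Section 2.5 names one precondition for allocation: "Once the participants and/or their legal representatives have signed the informed consent, they will be randomized". It does not require a baseline assessment first. One researcher holds the allocation and is the person "who will be responsible for communicating the assigned intervention to the participants and/or their families via a telephone call". The section gives no date for that call relative to baseline or to the first session.

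On blinding, section 2.5 states that "neither the patient nor the professional administering the rESWT sessions can be blinded", whereas "the evaluating physiotherapist and their assistant will be blinded throughout the entire intervention". It adds one safeguard for the visits: "Instructions will also be given to the patient and their family not to discuss the received treatment during assessments".

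Section 2.7 places t0 relative to treatment, not relative to allocation: "Prior to the first rESWT session, the blinded evaluating physiotherapist and his assistant will conduct a baseline assessment (t0"). The same sentence includes reference information for judging goal achievement. Section 2.8.2 describes how the GAS yardstick is made: "Once the objectives of shock wave application are agreed upon with the patient and/or family", expectations are then set for each objective, and attainment is scored from −2 to +2 around them.

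Table 1 (section 2.1) marks consent under −24 weeks and allocation under 0. The first marks for MTS, GAS, TUG, 10MWT and pSWE stand under week 1, the column that also holds the first session of all three groups.

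**The concern.** A baseline is protected from knowledge of the arm if it is recorded before randomization, or at least before the arm is known. Here the stated order is consent, allocation, baseline, with unblinded patients and no rule on when they are told.

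This matters most for GAS. A GAS score is the distance from an expected level that the patient or family helps to set. A family that knows its sessions are spread over a shorter or longer period may expect a different amount or timing of change. An easier or harder expectation changes the score even if the clinical course is the same. Blinding the evaluator limits this but does not remove it, because the other party to the agreement may know the arm. The discussion presents GAS as a distinguishing feature of the study, so the result will be noticed.

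TUG and 10MWT are timed walks at the fastest pace short of running. Effort at baseline could also respond to knowledge of the arm, though less directly.

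There is a second, smaller consequence. Section 2.4 lets participants withdraw at any time, and section 2.12 plans an intention-to-treat analysis. A patient who leaves after allocation but before t0 is randomized and has no baseline.

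**Working it through.** The point concerns the order of events. The plan gives no figure to reproduce, so the check sets the relevant statements side by side.

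| Step | Where stated | Timing given |
|---|---|---|
| Consent | 2.5; Table 1 | −24 weeks |
| Randomization | 2.5; Table 1 | after consent; allocation at 0 |
| Telephone disclosure | 2.5 | none |
| t0 (all outcomes) | 2.7; Table 1 | before the first session; week 1 |
| GAS goals and expectations | 2.8.2, with the goal reference in 2.7 | none relative to allocation |
| First session, all groups | Table 1 | week 1 |

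1. **Allocation against baseline.** Section 2.5 and Table 1 agree that allocation comes first. This order is stated, so it is not a detail left to another document.
2. **Disclosure against baseline.** The call cannot precede allocation. The text allows it before or after t0. Nothing in sections 2.5, 2.7 or 2.8.2 holds it back.
3. **What a family could know.** By Table 1 the sessions fall in weeks 1, 2 and 3 (control), 1, 3 and 5 (Group A) and 1, 5 and 9 (Group B). First to last session spans 3 − 1 = 2, 5 − 1 = 4 and 9 − 1 = 8 weeks. At the week 3 assessment column the control group is at its third session, Group A is at its second, and Group B is between its first and second. A family told its arm has a concrete reason to expect a different course.
4. **Which outcomes are exposed.** GAS is exposed most, because the expectation is the scale. TUG and 10MWT (2.8.3, 2.8.4) are exposed through effort. MTS (2.8.1) is a passive-stretch angle taken by a blinded evaluator, and pSWE (2.8.5) is an instrument reading. Both are largely unaffected.
5. **How GAS would respond (assumption only).** If a share *p* of one arm set a goal one full level easier, and no score were capped at the end of the scale, that arm's mean for the goal would shift by *p* × 1. For *p* = 0.20 this is 0.20 × 1 = 0.2, and for *p* = 0.40 it is 0.40 × 1 = 0.4. If the goals were harder, the shifts would be −0.2 and −0.4. The document supports neither the shares nor the sign.
6. **Withdrawal before t0.** Section 2.11 assumes 10% loss to follow-up in total and does not say how much falls before t0, so the number affected cannot be computed.

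**The case against.** The strongest objection is that the document never says families know their group at baseline. Allocation is not disclosure. All groups have their first session in the same week, so the visit can be booked without revealing the arm, and the call could follow t0. The flow diagram is not available here, and an article condenses a longer protocol. This stands: a reader might infer from Table 1 that families have been told before t0, but the text does not establish it. What remains is that the plan allows that order and contains no safeguard against it.

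Further objections also carry weight:

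- A blinded physiotherapist conducts t0, and families are told not to discuss treatment at assessments. This limits drift in goal difficulty and protects the evaluator's blinding. It does not neutralize what a family already expects.
- All groups receive three active sessions with the same settings (section 2.6), so differences in expectation may be modest. A reader might infer a bias in favour of the longer intervals, but families who hope for more could equally set harder goals.
- A reader might infer that a contaminated baseline enters the model as a covariate. Section 2.12 names age, sex, GMFCS and comorbidities, not the baseline outcome value, so that step is unsupported.
- A reader might extend the concern to the primary outcome. The nature of the MTS measurement and the evaluator's blinding argue against that.

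**Conclusion.** The point holds in a limited form. As written, allocation precedes baseline, patients and families are unblinded, and nothing defers the undated call until t0 is complete. GAS goals and expected levels, and to a lesser extent the TUG and 10MWT baselines, can therefore be set with knowledge of the arm. Any patient who withdraws between allocation and t0 also lacks a baseline for the intention-to-treat analysis.

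The exposure lies in secondary outcomes. Its size and direction cannot be derived from the document, and the shifts of 0.2 and 0.4 only illustrate how the scale responds under assumed shares. The conclusion rests on reading Table 1's columns as a time order, which section 2.5 supports, and on the absence of any stated rule about disclosure. It is a weakness worth correcting because the correction is cheap. It does not show that bias will occur.

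**What to change.** Complete t0 after consent and before randomization, and record the GAS goals and expected levels in writing and lock them at that point. If that order is impractical, the minimum is to complete and lock both before the allocation call. State the rule in sections 2.5 and 2.7, and move allocation after the baseline assessment in Table 1 (or show disclosure as a separate, later entry).

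The cost is scheduling. Table 1 places t0 and the first session in the same column and does not say whether they share a visit. If they do, t0 may have to be held slightly earlier, which could mean a separate attendance, or the call made after t0. The common first-session week makes the later call feasible. No new measurement, staff or treatment change is needed.

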### Interventions

2.6

Each patient will receive 2000 impulses in the Triceps Sural muscle (distributed by all the plantar flexor muscles: soleus and gastrocnemius), at a 2.2 Bars pressure and a frequency of 8 Hz. For the application of the therapy the patient will be positioned lying face down on a stretcher. Conductive gel will be applied, and a sweeping motion will be performed across the entire area to be treated. The application will have a duration of 4 min for each muscle group. In patients with bilateral involvement, treatment will be administered to both extremities. The application of rESTW does not require analgesia, sedation or anesthesia. No adverse effects are expected from the intervention beyond those observed in only two studies, such as temporary skin redness, petechiae, or superficial small hematomas that resolve within a few days after application (16, 21).

The Control Group will receive 3 rESWT sessions with a time interval of 1 week between each session.

The Experimental Group A will receive 3 rESTW sessions with a time interval of 2 weeks between each session.

The Experimental Group B will receive 3 rESTW sessions with a time interval of 4 weeks between each session.

For treatment in all groups, the same device and probe will always be used: the Swiss Dolor Clast Smart model, which guarantees cavitation at any frequency, from the company EMS (Electro Medical System) based in Nyon, Switzerland. The equipment complies with all European safety regulations required for medical devices. Registration: EN-60601-1, Class I. Type BF IP40. 93/42 EEC.

During the course of the study and the follow-up period, patients will not be able to receive botulinum toxin treatment and/or focal intramuscular treatment with phenol or alcohol in the Triceps Sural or any other muscle of the lower extremity. All patients will continue to undergo their regular physiotherapy sessions or physical activity. The type of exercises performed and the total hours per week will be recorded.

### Outcome measures

2.7

Primary outcome measures: Spasticity of the treated muscles assessed with the Modified Tardieu Scale (MTS). Secondary outcome measures: Goal Attainment Scale (GAS), Timed Up and Go Test (TUG), 10 Meter Walk Test (10-MWT), Point shear wave elastography (pSWE), satisfaction with the therapy, and adverse effects. Prior to the first rESWT session, the blinded evaluating physiotherapist and his assistant will conduct a baseline assessment (t0) of all outcome variables and other aspects deemed appropriate as reference for assessing goal achievement. These assessments will be repeated across all intervention groups at 3 weeks from the start of treatment (t1), 5 weeks from the start of treatment (t2), 9 weeks from the start of treatment (t3), 12 weeks from the start of treatment (t4), and 24 weeks from the start of treatment (t5).

### Clinical assessments

2.8

#### Modified Tardieu Scale

2.8.1

The main variable of the study will be the physiological response of spasticity in the treated muscle, assessed using the Modified Tardieu Scale (MTS). This test is based on the evaluation of muscular resistance to passive stretching at two different speeds: slow speed (V1) and fast speed (V3), to quantify the joint angles at which such resistance appears. The V1 stretch is used to determine the angle of muscle resistance at low speed (R2), equivalent to the passive range of motion (pROM) and the V3 stretch is used to determine muscle resistance at high speed (R1) or catch reflex. The MTS it could be more sensitive than other measures in assessing spasticity. Its inter- and intra-rater reproducibility is acceptable (25). All measurements were conducted using a inclinometer to determine the angular value of the two segments. For the measurement of calf muscles, separate stretches were applied to the gastrocnemius muscle (measured with the knee extended) and the soleus muscle (measured with the knee flexed at 90°).

#### Goal attainment scaling

2.8.2

The Goal Attainment Scaling (GAS) is an individualized and patient-centered scale in which specific goals (one main and one secondary in our case) are proposed with concrete expectations for each patient. It provides two types of information: quantitative (assessment of success) and qualitative (what the patient aims to achieve). Once the objectives of shock wave application are agreed upon with the patient and/or family, such as improving function, gait, pain, perceived spasticity sensation, or enhancing orthosis tolerance, improvement expectations will be determined for each objective. It will be assessed whether these expectations have been met (0), are better (+1), much better (+2), worse (−1), or much worse (−2) than expected. It is a highly dynamic scale that allows quantifying any set objective. It is possibly the scale that best aligns clinical practice with patient expectations (26).

#### Timed up and go test

2.8.3

The functional response in improving the overall patient mobility will be assessed using the Timed Up and Go Test (TUG), where the time it took for the person to stand up from a chair, walk 3 meters, return, and sit back down with their back against the chair (27). The time will be measured in seconds with a stopwatch. The patients will undergo the test twice with the instruction to “walk as fast as they can without running.” The best recorded time will be documented.

#### 10 Meter Walk Test

2.8.4

The functional response in improving gait will be evaluated with the 10 Meter Walk Test (10MWT), where the time it took for the person to walk 10 meters in a straight line will recorded (28). The patients will undergo the test twice with the instruction to “walk as fast as they can without running.” The best recorded time will be documented.

#### Point shear wave elastography

2.8.5

Elastography by ultrasound is a non-invasive imaging technique that measures tissue displacement, i.e., tension in response to the application of a specific force. The Point Shear Wave Elastography (pSWE) measures the acoustic force impulse transmitted perpendicular to the tissue, providing a value in kPa based on the greater or lesser deformity of the explored tissue (29). The muscular stiffness of the soleus and gastrocnemius muscles will be assessed. The Aplio a550 device from Canon Medical Systems SA will be used to perform the measurements.

#### Satisfaction with the therapy

2.8.6

A satisfaction questionnaire will be administered to assess the level of satisfaction with the treatment among all patients and/or legal guardians.

### Adverse effects

2.9

If adverse effects arise from any of the interventions, they will be systematically recorded and documented in the data collection notebook specifically created for the study.

### Data management

2.10

All data will be recorded and stored in the Data Collection Notebook (DCN). These will be kept in a locked cabinet by the person responsible for clinical assessments. All data will be recorded in an ACCESS-type database with input coding. The first section: Will collect all the baseline personal information of the patient: age, sex, type of CP, and description according to the guidelines of the European CP Registry using the GMFCS. The second section: Will collect all the information related to baseline assessments and temporal assessments of each variable. In this part of the notebook, only the evaluating physiotherapist will have access. The third section: Will collect all the information regarding any adverse effects that may appear during the study.

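### The sole evaluator alone has access to each patient's earlier readings, and nothing masks those values, so examiner-dependent Tardieu angles could be anchored on previous visits and blur how benefit fades

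*Protocol article*

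**What the plan says.** Three parts of the protocol article bear on this.

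- **Section 2.10, Data management.** The notebook's second section is described thus: "Will collect all the information related to baseline assessments and temporal assessments of each variable". Access is then limited: "In this part of the notebook, only the evaluating physiotherapist will have access". On custody of the records: "These will be kept in a locked cabinet by the person responsible for clinical assessments".
- **Section 2.5, Randomization, blinding and treatment allocation.** There is one assessor for the whole trial: "The evaluating physiotherapist will always be the same and will be unaware of the origin of the intervention group to which the patient belongs". The blinding statement is that "the evaluating physiotherapist and their assistant will be blinded throughout the entire intervention". The safeguards that follow (allocation section withheld until follow-up of the last patient is complete, no questions about treatment, separate rooms) all concern treatment group.
- **Section 2.8.1, Modified Tardieu Scale.** The primary outcome is the angle at which resistance appears during a passive stretch. R2 comes from the slow stretch; for the fast one, "the V3 stretch is used to determine muscle resistance at high speed (R1) or catch reflex". The angle is read with an inclinometer.

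Section 2.7 repeats the assessments at weeks 3, 5, 9, 12 and 24 (t1 to t5) after baseline (t0).

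**The concern.** The only person given access to a patient's earlier angles is the person about to judge the next one. The inclinometer gives the number, but the examiner decides when resistance or the catch has been reached. A rater who knows the last value can drift towards it without intending to. Blinding to group, even if perfect, does not prevent this.

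The trial asks how long benefit lasts, and follow-up runs to 24 weeks so that the arms have time to separate. Carry-over from one visit to the next acts on exactly that feature of the data: it smooths the time course, so loss of benefit shows late and differences between arms are partly averaged away. It cannot be repaired in the analysis, because the unanchored reading was never recorded.

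**Working it through.** **What the text establishes**

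1. Earlier and later readings of each variable share one section (2.10).
2. The evaluator has sole access to that section, and the notebook is kept by the person responsible for clinical assessments (2.10).
3. The same evaluator measures every patient (2.5).
4. Access restrictions by section are already in use, but the one applied to the evaluator covers allocation only (2.5).
5. Earlier material has a legitimate use at later visits. Goal Attainment Scaling is scored against expectations agreed beforehand (2.8.2), and section 2.7 collects baseline information as a reference for it.

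Anchoring is therefore possible under the stated arrangement. Whether it would happen, and how strongly, is not stated.

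**Size: an illustration**

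The plan has no figure for this effect. Assume that each recorded gain mixes the true gain with the previous recorded gain:

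r_k = (1 − w) × true_k + w × r_(k−1), with r_0 = 0.

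The weight w is an assumption, taken as 0.1 to 0.3. The 5-degree gain is the target difference in section 2.11.

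*Case A: true gain 5, 5, 5, 5, 0 degrees at t1 to t5 (all lost between weeks 12 and 24).*

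| w | t1 | t2 | t3 | t4 | t5 |
|---|---|---|---|---|---|
| 0.1 | 4.50 | 4.95 | 5.00 | 5.00 | 0.50 |
| 0.2 | 4.00 | 4.80 | 4.96 | 4.99 | 1.00 |
| 0.3 | 3.50 | 4.55 | 4.87 | 4.96 | 1.49 |

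A vanished gain still reads 0.5 to 1.5 degrees at t5, and the first gain is under-read by the same amount. If another arm truly keeps 5 degrees throughout, both arms have the same history up to t4, so the recorded difference at t5 is (1 − w) × 5 = 4.5, 4.0 or 3.5 degrees instead of 5.

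*Case B: different time courses, no true benefit in either arm at week 24.* Assumed true gains are 5, 5, 4, 2, 0 for control (gradual fading) and 2, 4, 6, 5, 0 for Group B (late loss).

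| w | Control, week 24 | Group B, week 24 | Spurious difference, week 24 | Week-12 difference (true 3.0) |
|---|---|---|---|---|
| 0.1 | 0.22 | 0.51 | 0.29 | 2.87 |
| 0.2 | 0.49 | 1.02 | 0.53 | 2.67 |
| 0.3 | 0.79 | 1.51 | 0.72 | 2.40 |

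The gradually fading arm carries over about half as much as in Case A; the arm that loses everything in the last interval carries over about the same.

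**Effect on a week-24 comparison**

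From section 2.11 (SD 16.44, correlation 0.91), the SD of change is 16.44 × √(2 × (1 − 0.91)) = 6.975. With this SD, 2 × (6.975 × (1.645 + 0.842) / 5)² = 24.06, which agrees with the plan's 24 per group as a one-sided figure before losses. The standard error of a difference with 24 per group is 6.975 × √(2/24) = 2.01 degrees.

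- Case B, two-sided 5% test: the rejection rate rises from 5.0% to 5.2%, 5.8% and 6.5% for w = 0.1, 0.2 and 0.3.
- Case A, true difference 5 degrees: two-sided power falls from about 70% to about 61%, 51% and 41%. This holds the SD fixed. Anchoring may also reduce the SD, so these figures are indicative only.

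**The case against.** The strongest reply is that the access sentence is a confidentiality rule. It says who may open the section, not that earlier angles are open during a measurement, that visits share a page, or that the evaluator looks back. A reader might infer that the evaluator works from the earlier values at each visit. The article does not say so, and that reading should not be adopted. Page layout and who writes down the angle may well be set out in a fuller document. This part of the objection stands, and it limits the point to a possibility that the arrangement leaves open. It does not remove the point, because shared filing, sole access and one evaluator are stated, not inferred from silence.

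A reader might also infer that the trial would overstate how long benefit lasts. The direction is conditional. Carry-over makes a fading gain look more lasting, but it also under-reads early gains and shrinks true differences between arms. Since one evaluator blinded to group rates all arms, the between-arm result is often dilution. A spurious advantage for a later-treated arm is possible but small in the example above.

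It is also fair to say that the size rests wholly on an assumed w, that Case A puts the whole loss into the last interval, and that the assistant's role in reading or recording is not described, so current practice may already be close to the fix. Finally, withholding every earlier sheet would take away what is needed to score Goal Attainment Scaling. That objection is right, and the fix makes an exception for it.

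**Conclusion.** The point holds as a weakness in the stated arrangement, not as a demonstrated bias. The sole evaluator alone has access to all earlier readings, the blinding rules cover allocation only, and the primary outcome depends on the examiner's judgement. Earlier values could therefore anchor later ones and blur the decay of benefit that the trial sets out to measure.

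The size is unknown. Under an assumed 10 to 30% carry-over, a 5-degree gain lost between t4 and t5 would still read 0.5 to 1.5 degrees, and a gradually fading gain 0.2 to 0.8 degrees. A true 5-degree difference at t5 could read 4.5 to 3.5 degrees. With no true difference, the time courses assumed above produce a spurious 0.3 to 0.7 degrees. No value of w and none of these time courses comes from the documents. Nothing here suggests that the evaluator would learn the treatment group. The change is worth making because it is cheap and cannot be made after the readings are taken.

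**What to change.** - **Section 2.10.** Record the Modified Tardieu angles, and other examiner-dependent measures, on a separate sheet for each visit. After the visit the sheet goes to a team member not involved in assessment and is unavailable to the evaluator until that patient's follow-up ends.
- **Section 2.8.1.** State that the evaluator moves the limb and calls the point of resistance, and that the assistant already present reads the inclinometer and writes down the angle.
- **Goal Attainment Scaling.** Keep the agreed goals and expectation levels on their own sheet, which stays available at every visit.

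The cost is a change of paper forms and a sentence or two in each section, with no extra staff, visits or procedures. The downside is that an outlying angle can no longer be checked against earlier ones on the spot.
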